**Methods/design:**

In this prospective, single-center, double-blinded, randomized controlled trial, 214 patients undergoing reoperation or multiple valve surgery are randomly allocated to either the iron isomaltoside 1000 (IVFe) or the control group from August 2016 to August 2018. The IVFe group receives iron isomaltoside 1000 mg (maximum dose 20 mg/kg) intravenously 3 days before and after the surgery. The control group receives an equivalent volume of normal saline. The primary endpoint is transfusion requirement (more than 1 unit of packed erythrocytes) for postoperative care until discharge and secondary endpoint are major complications, such as delayed ventilator therapy, acute kidney injury, and mortality. Reticulocyte count, plasma hepcidin, iron profiles (serum iron, serum ferritin, total iron-binding capacity, transferrin, transferrin saturation), coagulation profiles, urinary analysis, and chemical profiles are measured for three preoperative baseline-data days and just before surgery, except for hepcidin. After surgery, daily routine basic laboratory tests are measured just before discharge and reticulocyte count, iron profiles, and hepcidin are repeatedly checked for three postoperative days.

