### Withdrawal and dropout

All participants will have the right to withdraw from the study at any time. Participation will be terminated if the individual wants to stop and withdraws consent. The trial will be stopped if the investigator believes that there are unacceptable risks to participants. If any patients show typical complications of IVFe, such as nausea, vomiting, hypotension, gastric discomfort, urticaria, and acute renal failure, participation will be terminated immediately. The patients who have Hb concentrations higher than 8 mg/dl postoperatively, yet require transfusion due to symptoms of acute anemia, such as shortness of breath, change in respiratory rate and pulse rate, mental function deterioration, and myocardial ischemia, are excluded from the study. Patients with postoperative paravalvular leakage should be removed to avoid confusion with the possibly similar effects on red blood cells as hemolytic anemia. Postoperative gastrointestinal bleeding is excluded. We also excluded patients who underwent re-exploration for postoperative bleeding (postoperative bleeding is defined as total drainage volume < 1000 cm^3^ during the 4 h after arrival in the intensive care unit (ICU)).

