### Study objective and outcomes (primary and secondary outcomes)

The primary objective of the trial is to demonstrate that IVFe is superior compared to placebo in leading to less decrease in the Hb level and reducing the need of transfusion in patients undergoing complex cardiac surgery, which is a highly possible scenario for receiving a transfusion. The secondary objectives are to compare the effects of IVFe on the clinical (or surgical) outcomes (e.g., renal failure, respiratory failure, etc.) from reducing the need for blood transfusion and the stability of iron-related parameters. The final objective is to assess the role of the iron-regulatory protein, hepcidin, as a biomarker, as well as any association of hematological parameters with outcome. Thus, we decided the endpoints as followings: the primary endpoint is the comparison of perioperative transfusion requirements in terms of overall incidence and mean amounts of units of packed erythrocytes transfused per patient during and after the operation until discharge, and the secondary endpoint is the occurrence of postoperative major advanced complications (delayed ventilator therapy, AKI and all-cause mortality). A Hb concentration of less than 7 mg/dl during CPB, and less than 8 mg/dl after CPB and postoperatively, were used as transfusion thresholds. Intraoperatively, we measured the Hb concentration post induction and every 30 min during CPB, then at 10 min post CPB and post sternal closure, and postoperatively at the time of, and 8 h after, arrival at the ICU. After the day of surgery, we measured the Hb concentration in the morning if there was no excessive bleeding (over 1000 cm^3^) or symptoms of anemia. Any patients who have Hb concentrations higher than 8 mg/dl postoperatively, yet required transfusion due to symptoms of acute anemia, such as shortness of breath, change in respiratory rate and pulse rate, mental function deterioration, and myocardial ischemia, were excluded from the study. We also excluded patients who had undergone re-exploration for postoperative bleeding (postoperative bleeding was defined by total drainage volume (< 1000 cm^3^) during the 4 h after arrival in ICU).

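### Randomised patients who are transfused for symptoms with Hb above 8 are excluded, which deletes primary-endpoint events; further post-randomisation removals may also differ by arm

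*Protocol article*

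**What the plan says.** The section on study objective and outcomes defines the primary endpoint as "transfusion requirements in terms of overall incidence and mean amounts of units of packed erythrocytes transfused per patient", covering the operation and the time until discharge. The Abstract words it differently: "The primary endpoint is transfusion requirement (more than 1 unit of packed erythrocytes) for postoperative care until discharge".

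Withdrawal and dropout then lists events after which a randomised patient leaves the study:

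- Transfusion for symptoms above the Hb threshold. The rule covers "The patients who have Hb concentrations higher than 8 mg/dl postoperatively, yet require transfusion due to symptoms of acute anemia" (unit as printed).
- Paravalvular leak: "Patients with postoperative paravalvular leakage should be removed".
- Gastrointestinal bleeding: "Postoperative gastrointestinal bleeding is excluded".
- Re-exploration for postoperative bleeding.
- Typical complications of the iron product, from nausea to acute renal failure, after which "participation will be terminated immediately".

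Two of these rules appear again beside the primary endpoint in the outcomes section: "Any patients who have Hb concentrations higher than 8 mg/dl postoperatively, yet required transfusion due to symptoms of acute anemia", with the listed symptoms, "were excluded from the study. We also excluded patients who had undergone re-exploration for postoperative bleeding".

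Allocation follows consent (Participants and eligibility criteria), and the first infusion is given 3 days before surgery (Intervention). The four postoperative rules therefore act after randomisation and after the scheduled first infusion. The complication rule acts after treatment has begun. Nothing in the article says that only study infusions stop, or that these patients stay in follow-up and analysis.

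**The concern.** A trial that asks whether iron reduces transfusion should not drop patients because they were transfused. The symptom rule does this directly: a patient meets it only by needing the treatment that the endpoint counts.

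The rule also depends on the Hb level at the time of transfusion, and the stated primary objective is that iron limits the fall in Hb. If iron works as hoped, a transfused patient in the iron group may be more likely to be above 8, and so more likely to be removed, than a transfused control patient. The complication rule is written around reactions to the active drug, so it too may act unequally. It also lists acute renal failure, which overlaps acute kidney injury, a secondary endpoint.

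At stake is whether the analysed groups are still the randomised groups, and whether an observed difference reflects less transfusion or a different pattern of removal.

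**Working it through.** **Inputs from the article.** Sample size gives a transfusion rate of 40%, a 35% reduction reported earlier, 97 patients per group raised to 107 for 10% dropout, and a two-sided 5% test. Statistical methods gives a chi-square or Fisher's exact test for dichotomous variables. No removal rate is stated anywhere, so every removal fraction below is an assumption.

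**The plan's own allowance.** 97 × 1.10 = 106.7, which rounds to 107, so the dropout step reproduces. If 10% per arm were removed, 107 × 0.90 = 96.3 would remain, so a removal of that size would use the whole allowance. The allowance replaces numbers. It does not restore comparability.

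**Illustration with no true effect.** Let t be the proportion transfused at the threshold and s the proportion transfused for symptoms above it and then removed, with t + s = 40% in both arms.

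Analysed rate = t / (1 − s); analysed n = 107 × (1 − s).

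For 35+5 (control) against 25+15 (IVFe):
- Control: 0.35/0.95 = 36.8%, n = 101.65.
- IVFe: 0.25/0.85 = 29.4%, n = 90.95.
- Difference: 7.4 points.
- Pooled rate: (0.35 + 0.25)/(0.95 + 0.85) = 0.333. Null standard error: √[0.333 × 0.667 × (1/101.65 + 1/90.95)] = 0.0680.
- Unpooled standard error: √[0.368 × 0.632/101.65 + 0.294 × 0.706/90.95] = 0.0676.
- Rejection probability: Φ[(0.0743 − 1.96 × 0.0680)/0.0676] plus a negligible lower tail, which is about 19%.

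The same steps for other splits:

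| Control t+s | IVFe t+s | Analysed rates | Difference (control − IVFe) | Rejection at nominal 5% |
|---|---|---|---|---|
| 35+5 | 35+5 | 36.8% vs 36.8% | 0 | 5.0% |
| 36+4 | 34+6 | 37.5% vs 36.2% | 1.3 points | 5.4% |
| 35+5 | 30+10 | 36.8% vs 33.3% | 3.5 points | 8% |
| 35+5 | 25+15 | 36.8% vs 29.4% | 7.4 points | 19% |
| 30+10 | 35+5 | 33.3% vs 36.8% | −3.5 points (against iron) | 8% |

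**Illustration with a true effect and equal removal.** Take 40% against 26% (0.40 × 0.65 = 0.26) and remove 20% of transfused patients in each arm. The observed rate is p(1 − f)/(1 − pf):
- Control: 0.32/0.92 = 34.8%.
- IVFe: 0.208/0.948 = 21.9%.
- The difference shrinks from 14.0 to 12.8 points (on unrounded rates), and power at 107 randomised per arm falls from 0.59 to 0.52.
- The arms lose different numbers: 107 × 0.40 × 0.20 = 8.6 against 107 × 0.26 × 0.20 = 5.6.

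So even an even-handed rule costs events and power when iron works.

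**A contradiction within one removal rule.** Both sections that exclude re-exploration define postoperative bleeding as drainage below 1000 cm³ in the first 4 hours in intensive care. The outcomes section elsewhere treats more than 1000 cm³ as excessive bleeding. These passages must be reconciled, because the definition bears on who is removed.

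**The case against.** Several points on the other side stand.

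- Only the symptom-transfusion rule removes a patient for the outcome itself. Re-exploration and gastrointestinal bleeding are causes of transfusion, paravalvular leak is linked to it through hemolysis, and nausea or urticaria is a drug reaction. A reader might infer that all five rules delete endpoint events by definition. The text does not support that. Nor does it give any reason to think that paravalvular leak depends on treatment; for that rule the concern is lost patients and a narrower population.
- Under the Abstract's wording, a patient given a single unit for symptoms has no primary event. The deletion is complete only under the outcomes section's wording.
- The trial is double-blind with a saline control, so the rules should be applied without knowledge of the arm, and equal removal under no effect leaves the error rate at 5%. Blinding reduces discretionary removal. It cannot stop Hb level or drug reactions from depending on treatment.
- The illustration holds total transfusion at 40%, so every threshold transfusion that iron avoids becomes a symptom transfusion. Iron might reduce symptoms as well. The split also ignores transfusion during surgery, which counts towards the endpoint but does not itself trigger the symptom rule.
- Analysis populations are often left to a fuller document. Here, however, the article itself states that these patients are excluded or removed, so this is a stated rule and not an omission.

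**Conclusion.** The concern holds for what the article states. Randomised patients are excluded for a transfusion that the primary endpoint counts, and others are removed for bleeding, leak or drug reactions after randomisation and treatment. The loss of endpoint events follows from the wording, with the one-unit qualification under the Abstract's definition.

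Bias in the comparison is a risk, not an established result. With no true effect it needs removal that differs by arm, and the documents give no rates from which its size or direction could be worked out. In the assumed splits it runs from nothing (5% rejection) to 7.4 points in favour of iron (19%), and it can go against iron. A reader might infer that the plan is bound to manufacture a benefit, or that the trial can no longer answer its question. The documents do not support either reading. What they do show is that the rules change the population and the quantity estimated, and leave a positive or negative result open to an explanation that the design should have ruled out.

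**What to change.** - Make the primary analysis all randomised patients, analysed as randomised, and count every packed-erythrocyte transfusion whatever its trigger. Restricting to those who undergo surgery would itself be a selection made after the first infusion.
- Continue outcome collection to discharge for patients who meet any of these rules or stop study infusions, unless they withdraw consent. This concerns follow-up and analysis only; no clinical stopping rule or transfusion threshold needs to change.
- For patients already removed, recover in-hospital transfusion data where consent allows.
- Report the analysis without these patients, and threshold-triggered transfusion only, as labelled sensitivity analyses.
- Reconcile the two statements about the 1000 cm³ drainage volume.

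The cost is modest but not nil. It needs an amendment while recruitment is still open (Study status) and retrieval of records for patients already removed, some of whose data may be missing. Counting bleeding-driven transfusions unrelated to iron will add some noise. The Data collection section already plans to gather clinical data on all enrolled patients during admission, so prospective collection should add little.

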### Intervention

IVFe administration is scheduled twice, at 3 days before and after surgery, regardless of Hb level. The IVFe group receives iron isomaltoside 1000 as a single-dose infusion of 1000 mg over 30 min with a maximum single dose of 20 mg/kg. The placebo group receives saline (0.9% Sodium Chloride Injection; JW Pharmaceutical, Seoul, Korea) as a single-dose infusion of 100 ml over 30 min.

### Study objective and outcomes (primary and secondary outcomes)

The primary objective of the trial is to demonstrate that IVFe is superior compared to placebo in leading to less decrease in the Hb level and reducing the need of transfusion in patients undergoing complex cardiac surgery, which is a highly possible scenario for receiving a transfusion. The secondary objectives are to compare the effects of IVFe on the clinical (or surgical) outcomes (e.g., renal failure, respiratory failure, etc.) from reducing the need for blood transfusion and the stability of iron-related parameters. The final objective is to assess the role of the iron-regulatory protein, hepcidin, as a biomarker, as well as any association of hematological parameters with outcome. Thus, we decided the endpoints as followings: the primary endpoint is the comparison of perioperative transfusion requirements in terms of overall incidence and mean amounts of units of packed erythrocytes transfused per patient during and after the operation until discharge, and the secondary endpoint is the occurrence of postoperative major advanced complications (delayed ventilator therapy, AKI and all-cause mortality). A Hb concentration of less than 7 mg/dl during CPB, and less than 8 mg/dl after CPB and postoperatively, were used as transfusion thresholds. Intraoperatively, we measured the Hb concentration post induction and every 30 min during CPB, then at 10 min post CPB and post sternal closure, and postoperatively at the time of, and 8 h after, arrival at the ICU. After the day of surgery, we measured the Hb concentration in the morning if there was no excessive bleeding (over 1000 cm^3^) or symptoms of anemia. Any patients who have Hb concentrations higher than 8 mg/dl postoperatively, yet required transfusion due to symptoms of acute anemia, such as shortness of breath, change in respiratory rate and pulse rate, mental function deterioration, and myocardial ischemia, were excluded from the study. We also excluded patients who had undergone re-exploration for postoperative bleeding (postoperative bleeding was defined by total drainage volume (< 1000 cm^3^) during the 4 h after arrival in ICU).

Postoperative variables included the amount of bleeding measured by chest-tube drainage after surgery, fluid input, urine output, and overall amount of ABT. Hb concentrations, PT, AST/ALT, and creatinine (Cr) levels were measured preoperatively, post anesthetic induction, and postoperative day (POD) 0 (day of the surgery after arrival in the ICU), 1, 2, 3, 4, and 7. Reticulocyte count and iron profiles were measured preoperatively and post anesthetic induction and at POD 3, and POD 10, and the changes in reticulocyte count from the baseline values were calculated. Postoperative variables also included the incidence of perioperative transfusion volume, the incidence of AKI within 48 h after surgery, new-onset AF after surgery, duration of ventilator care, ICU stay and hospital stay, and in-hospital mortality. Multiple ABT is defined as more than 1 unit of packed erythrocytes during the operation and until discharge. AKI is defined as elevation of serum Cr of ≥ 0.3 mg/dl or 50–200% from baseline using the modified Risk, Injury, Failure, Loss, and ESRD classification [14]. Surgical mortality is defined as all deaths that occur during the hospital stay or after hospital discharge but within 30 days postoperatively.

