### Exclusion criteria

Exclusion criteria are as followings: (1) patients who have critical anemia that cannot be corrected by only iron replacement therapy (Hb < 9 g/dl for women and Hb < 10 g/dl for men) such as aplastic anemia, (2) patients who have end-stage renal disease (ESRD) treated with erythropoietin or any concomitant medication for erythropoiesis, (3) patients with previous paravalvular leakage, because any ensuing hemolytic anemia cannot be corrected by iron replacement, (4) patients with a hyperallergic reaction to iron agents, and aplastic anemia, and (5) patients who have been treated in intensive care unit for severe cardiac dysfunction.

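### Hb thresholds for transfusion and for post-randomisation exclusion are printed in mg/dl, while the eligibility limits are in g/dl; the units must be reconciled

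*Protocol article*

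**What the plan says.** The section on study objective and outcomes fixes when blood is given. Its transfusion thresholds are "A Hb concentration of less than 7 mg/dl during CPB, and less than 8 mg/dl after CPB and postoperatively". The same section then removes a group of patients after randomisation: "Any patients who have Hb concentrations higher than 8 mg/dl postoperatively, yet required transfusion due to symptoms of acute anemia". The section on withdrawal and dropout repeats that removal: "The patients who have Hb concentrations higher than 8 mg/dl postoperatively, yet require transfusion due to symptoms of acute anemia".

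The only other Hb limits in the article are under Exclusion criteria, where critical anaemia is marked by "Hb < 9 g/dl for women and Hb < 10 g/dl for men".

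These thresholds bear on the main outcome, because "the primary endpoint is the comparison of perioperative transfusion requirements in terms of overall incidence and mean amounts of units of packed erythrocytes transfused".

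**The concern.** Hb is the same laboratory measurement before and after enrolment, yet the article uses one unit at entry and another for every rule that applies afterwards. The two units convert into each other, so using both is not in itself an error. The difficulty is that the numerals printed with mg/dl lie on a wholly different scale from the eligibility limits.

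Two things depend on the affected numbers. One is the rule guiding clinicians when to transfuse, and transfusions given are what the primary endpoint counts. The other is the boundary that decides which randomised patients are removed because they were transfused for symptoms above the threshold. If the text is wrong there, someone who audits adherence, programs a deviation check or repeats the trial has to replace the printed value with a guess.

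**Working it through.** **Inputs**

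| Rule | Section | As printed |
|---|---|---|
| Transfusion threshold during bypass | Study objective and outcomes | < 7 mg/dl |
| Transfusion threshold after bypass and postoperatively | Study objective and outcomes | < 8 mg/dl |
| Exclusion if transfused for symptoms | Study objective and outcomes | > 8 mg/dl |
| Exclusion if transfused for symptoms | Withdrawal and dropout | > 8 mg/dl |
| Eligibility limit, women | Exclusion criteria | 9 g/dl |
| Eligibility limit, men | Exclusion criteria | 10 g/dl |

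All four Hb thresholds that apply after enrolment are in mg/dl, and both that apply before it are in g/dl. The thresholds are stated values, not derived ones, so there is no calculation of the plan's own to reproduce.

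**Conversion** (1 g = 1000 mg)

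- 7 mg/dl = 7 / 1000 = 0.007 g/dl
- 8 mg/dl = 8 / 1000 = 0.008 g/dl
- 9 g/dl = 9 × 1000 = 9000 mg/dl
- 10 g/dl = 10 × 1000 = 10000 mg/dl

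**Distance between the two sets of limits**, taking the eligibility limits as the lowest Hb at entry:

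- Women: 9000 / 8 = 1125 times the printed postoperative threshold
- Men: 10000 / 8 = 1250 times

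A woman entering at the limit would have to lose 1 − 8/9000 = 99.9% of her Hb concentration to reach the printed value.

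**What the literal text then does**

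- Transfusion rule: no patient falls below 0.007 or 0.008 g/dl, so the trigger is never met.
- Exclusion rule: every postoperative Hb is above 0.008 g/dl, so the Hb condition no longer separates anyone. Every patient transfused postoperatively for acute-anaemia symptoms meets the exclusion, whatever the Hb.

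**Is it an extraction fault?** Unlikely. The unit occurs four times in running prose across two sections, g/dl is read correctly under Exclusion criteria, and mg/dl also appears as the creatinine unit in the definition of acute kidney injury. Nothing elsewhere settles the matter: the Hb column of Table 1, as extracted, carries no unit.

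**Size of the discrepancy.** If the numerals 7 and 8 were meant in the eligibility unit, they would be 7000 and 8000 mg/dl, and 8000 / 8 = 7000 / 7 = 1000. That factor depends on the assumption; the conflict between the sections does not.

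**The case against.** The strongest reply is that this is a self-evident slip. An Hb of 8 mg/dl is impossible in a patient, the eligibility limits show the intended scale, and nobody at the bedside would act on 0.008 g/dl. The article describes no programmed trigger, and its case report form is not shown. No design, analysis or sample-size decision depends on the unit. All of this stands, and it limits the weight of the point. It does not remove the error: the wrong unit is repeated at every place where these rules are given, and the article contains no correct statement of them.

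Several stronger readings are tempting, and the article does not support them.

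- A reader might infer that eligibility is affected, or that all patients would be misclassified. The eligibility limits are already in g/dl and carry no error, and the literal exclusion reaches only patients transfused postoperatively for symptoms.
- A reader might infer that the threshold produces the primary endpoint. It guides transfusion, but the endpoint counts transfusions actually given and is not computed from Hb against a cut-off. A misprinted unit does not alter the units of blood recorded.
- A reader might take the absence of any threshold-triggered transfusion as an expected result. It follows only if the text were applied or coded literally, and nothing shows that it was.

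Whether randomised patients should be removed because of how they came to be transfused is a separate question. It remains whatever the unit, and it adds no weight here.

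**Conclusion.** The point holds as an internal inconsistency in a decision rule. The transfusion thresholds and the post-randomisation exclusion boundary are wrong as written when set against the eligibility limits in the same article. Taken literally, the trigger is empty and the exclusion takes in every patient transfused postoperatively for symptoms.

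The size is a factor of 1000, on the assumption that the same numerals were meant in the eligibility unit. The effect on actual conduct is probably small, and the 97 per group (107 with dropout) is untouched. The text should be corrected because it misstates the rule guiding the transfusions that the primary endpoint counts, and the boundary of a removal after randomisation. Whether 7 and 8 are suitable clinical values is not judged here.

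**What to change.** Reconcile the Hb units across Exclusion criteria, Withdrawal and dropout, and Study objective and outcomes, so that all limits are stated on one scale and the transfusion rule agrees with both statements of the exclusion. Then confirm that the case report form, and any threshold or deviation check that exists, use the reconciled unit. No clinical threshold is proposed; the sponsor should state the one that was in force.

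The cost is a unit correction at four places in the text and a short check of the data-collection forms. The article reports that recruitment was still incomplete at submission, so at that stage the check could be made before analysis.

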### Sample size

Sample size estimation is based on the null and alternative hypotheses. In our study, the null hypothesis is that “IVFe has no significantly different effect on Hb level and transfusion need after complex cardiac surgery” and we want to prove that the null hypothesis is wrong for replacing the alternative hypothesis by the two-sided test method. Previous reports [15, 16] suggested a 35% reduction in transfusion rate using IVFe but we set a higher transfusion rate (40%) considering the complexity and severity of cardiac surgery. The sample size calculation was based on superiority analysis under the hypothesis that all data was normally distributed data. We set the significance level at 0.05, the power at 80%, and the effect size was 0.5. A two-sided test was used and consequentially 97 patients were need for each group; however, we set each group as 107 considering a 10% dropout rate (total 214).

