### Statistical methods

Continuous variables were shown as means ± standard deviation (SD) and dichotomous variables are shown as numbers (percentages). Between-group comparisons of continuous variables were performed using the independent Student *t* test. Dichotomous variables were compared using the chi-square or Fisher’s exact tests, as appropriate. *P* values < 0.05 will be considered statistically significant.

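### Hb is in the primary objective, but with only t tests at P < 0.05 and no named Hb day or summary, six to eight correlated Hb tests are left open

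*Protocol article*

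**What the plan says.** All references are to the Protocol article.

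- **Objective.** Under Study objective and outcomes, the trial is to show that "IVFe is superior compared to placebo in leading to less decrease in the Hb level and reducing the need of transfusion". The endpoint sentence in the same section is narrower and leaves Hb out: "the primary endpoint is the comparison of perioperative transfusion requirements in terms of overall incidence and mean amounts of units".
- **Null hypothesis.** Under Sample size: "IVFe has no significantly different effect on Hb level and transfusion need after complex cardiac surgery".
- **Schedule.** Under Study objective and outcomes: "Hb concentrations, PT, AST/ALT, and creatinine (Cr) levels were measured preoperatively, post anesthetic induction", and then at "postoperative day (POD) 0 (day of the surgery after arrival in the ICU), 1, 2, 3, 4, and 7". Study design adds laboratory visits at POD 10 or discharge and at postoperative week 4. It also places the POD 3 sample immediately before the second infusion.
- **Analysis.** Under Statistical methods: "Between-group comparisons of continuous variables were performed using the independent Student" t test, and P "values < 0.05 will be considered statistically significant". This is the only method given for comparing continuous variables.

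No Hb day, nadir, average or change score is named. A change from baseline is defined for the reticulocyte count, but not for Hb.

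**The concern.** A two-sample t test takes one value per patient, and this schedule yields six to eight postoperative Hb values per patient. With no value singled out, the most direct way to follow Statistical methods is one t test per sampling day, each judged at 0.05. A lower P value on any one day could then be presented as meeting the Hb half of the primary objective, although the chance of such a day arising without any effect is well above 5%. The objective also concerns a smaller fall in Hb, that is, a course over time from baseline, and no stated analysis addresses that course as a whole.

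**Working it through.** **Inputs from the document.** Six postoperative Hb days (POD 0, 1, 2, 3, 4, 7), or eight with POD 10/discharge and week 4. Two-sided level 0.05 per test. 97 per group before dropout. Table 1 also has rows for POD 5 and 6; they are not counted here, so eight is not an upper limit.

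**Input assumed.** The correlation between days within a patient is not given. I use 0.5 to 0.85, either equal for all pairs of days or decaying with the number of visits apart (AR(1)).

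**The plan's own figure.** The plan gives no error rate for Hb to reproduce. Its sample size inputs ("We set the significance level at 0.05, the power at 80%, and the effect size was 0.5") give n = 2(1.96 + 0.842)²/0.5² = 63 per group (64 by the exact t test), not 97. That is a separate matter. I use 97 below only as the stated group size.

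**Step 1: chance of at least one P < 0.05 with no effect.** With independent tests it would be 1 − 0.95⁶ = 26.5% for six and 1 − 0.95⁸ = 33.7% for eight. With correlated tests it is the probability that the largest of k correlated standard normal |z| values exceeds 1.96, found by simulation (400,000 draws):

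| Tests | Pattern | Correlation 0.5 | 0.7 | 0.85 |
|---|---|---|---|---|
| 6 | equal | 20.7% | 16.4% | 12.5% |
| 6 | AR(1) | 23.6% | 20.0% | 15.4% |
| 8 | equal | 25.1% | 19.1% | 13.9% |
| 8 | AR(1) | 29.8% | 25.1% | 18.9% |

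Counting the AR(1) lag in calendar days instead gives 24.1% for six tests at 0.5. For eight (POD 10 as day 10, week 4 as day 28) it gives 31.5%, so the upper ends are not exaggerated.

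**Step 2: effect of naming one contrast.** One pre-named Hb test has an error rate of 5%, whichever contrast is chosen.

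**Step 3: does the choice of contrast matter?** With equal correlation ρ, the mean of six days has variance (1 + 5ρ)/6 of a single day: 0.58 at 0.5, 0.75 at 0.7, 0.88 at 0.85. Power is about Φ(δ/√(2v/97) − 1.96), where δ is the effect on the contrast in SD units and v is its variance ratio. A single day with δ = 0.40 (v = 1) has 80%. For the six-day mean, with assumed effect shapes and ρ from 0.5 to 0.85:

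- constant effect of 0.40: δ = 0.40, power 95% to 85%;
- effect rising in proportion to the day, reaching 0.40 on POD 7: δ = 0.40 × (0+1+2+3+4+7)/(7 × 6) = 0.162, power 31% to 23%;
- effect of 0.40 on POD 4 and POD 7 only: δ = 0.40 × 2/6 = 0.133, power 23% to 17%.

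Averaging therefore helps if the effect is roughly constant, and costs power if it comes late. The second case is plausible here, because four of the six samples (POD 0 to 3) are drawn before the second infusion.

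**The case against.** The strongest reply is that nothing in the article says Hb will be tested day by day. The schedule is a list of measurements, and the analysis sentence is generic. A t test on one derived value, such as a change in Hb, would satisfy it equally. Further, no laboratory level is a primary or secondary endpoint, and models for non-endpoint laboratory data are commonly left to a full analysis plan, which is not shown. On this view, naming one Hb measure for the existing t test would be enough.

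Much of this stands. Day-by-day testing is what the text permits, not what it announces. For PT, AST/ALT and creatinine levels the point is minor. Naming one measure would by itself remove the multiplicity. What does not stand is treating Hb as incidental: the article itself puts it in the primary objective and the null hypothesis, and names a method that does not fit the serial data without a further choice that it does not make.

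Stronger readings that the document does not support:

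- *Late comparisons are biased because only patients still admitted are sampled.* The POD 10 or discharge visit most naturally samples early leavers at discharge, so it keeps them. POD 7 could be affected, but no discharge rate by then and no Hb-based discharge rule is given, so no size can be attached.
- *Pooling the days is bound to gain precision.* Step 3 shows that the benefit depends on the shape of the effect.
- *The 97 per group reflects a split of alpha over six days.* A level of 0.05/6 with effect size 0.5 does give 2(2.638 + 0.842)²/0.25 = 97, but the article sets the level at 0.05 and mentions no split, so the match looks coincidental.

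One limit remains: transfusion raises Hb, possibly more often in controls. A mixed model does not resolve that.

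**Conclusion.** The point holds for Hb. As written, the plan leaves six to eight correlated t tests open on a variable in the primary objective, with a chance of a spurious significant day of about 12.5% to 24% (six) or 14% to 30% (eight), against a nominal 5%. These figures assume a between-day correlation of 0.5 to 0.85 and that each day is tested at 0.05. A reader might infer that the main result of the trial is at risk. It is not: transfusion incidence and units, and the dichotomous complications, do not depend on how serial Hb is analyzed. The change is worth making because it is cheap and uses data already scheduled.

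**What to change.** In Statistical methods, analyze serial Hb with one linear mixed model: all scheduled postoperative values as outcomes; baseline Hb, arm, day and arm-by-day as fixed effects; unstructured covariance within patient. Take baseline from the visit before the first infusion, since the post-induction value already follows it.

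Name, before unblinding, one Hb contrast as the single test at 0.05, and report the other day-specific differences with confidence intervals as description only. Choose the contrast with the dosing schedule in mind: an average over POD 0 to 7 suits an effect expected to be roughly constant, while a later day or days suits one expected to build up after the second infusion. PT, AST/ALT and creatinine levels can be labeled descriptive.

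The cost is analysis wording and a slightly more complex model, with no new samples or patients. Study status says recruitment was still incomplete at submission, so the contrast could be fixed at that stage, before unblinding.
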